### Data collection

Clinical and demographic variables will be collected and reported including age, body mass index, ejection fraction and other aspects of advanced echocardiographic assessment, STS mortality score, and comorbidities (for example: history of myocardial infarction, congestive heart failure, diabetes, dyslipidemia, hypertension, stroke, peripheral vascular disease, and smoking from the predefined STS database Version 2.6). In addition, assessments will be made regarding functional Activities of Daily Living (ADL) and Geriatric Depression Scale (GDS).

All information collection will employ electronic case report forms, namely Research Electronic Data Capture [21]. REDCap is a secure, web-based application designed to support data capture for clinical trials that allows customized data collection fields to support individual trial needs. Members of the research team will be responsible for building and maintaining the electronic case report form (eCRF), as well as monitoring the data entry for completeness, timeliness and accuracy. Inter-rater reliability checks between multiple assessors will be performed throughout the study.

### Reporting of compliance and adverse events

A specialist within the research group will monitor protocol compliance, occurrence and reporting of adverse events to the IRB.

### Bio-specimen collection and processing

Biological specimens will be collected throughout the perioperative period. Blood, atrial tissue, and urine specimens will be collected intra-operatively, both at pre-bypass and post-bypass time points. Blood and urine specimens will also be collected at other time points in the perioperative period. These specimens will be used for analysis for biomarkers of oxidative stress and investigation of mechanistic pathways.

### Follow-up

Subjects will be contacted by telephone by trained study team members for 1, 3, and 6-month t-MoCA, ADL, and GDS assessments. For feasibility, the protocol allows for a time window of 7 days before and after the 1-month follow-up, and 14 days before or after the 3- and 6-month postoperative calls.

## Statistical analysis

### Sample size calculation

Using previous data [3], and assuming a cross walk between t-MoCA and Mini-Mental State Examination (MMSE) [22], a two-sided α = 0.05 and 80% power, we will need 74 subjects in total to detect a mean difference in t-MoCA scores of 2 (standard deviation of 3) between the hyperoxia and normoxia group at postoperative day 2. This cognitive decrement was previously reported as clinically significant and postoperative day 2 was reported as the in-hospital postoperative nadir time point [19]. A total of 100 randomized subjects who have undergone the entire intraoperative intervention will be enrolled to allow for potential attrition from loss to follow-up or withdrawal.

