## Methods/design

### Study design

To assess the relationship between intraoperative arterial partial pressure of oxygen (PaO_2_) and the incidence of POCD and delirium we have designed a single-center, randomized, double-blind superiority trial of 100 participants with an allocation of 1:1. Subjects undergoing CABG surgery with CPB will be prospectively randomized to one of two different levels of fraction of inspired oxygen (FiO_2_) intraoperatively. The primary outcome of postoperative cognitive decline will be assessed via cognitive testing at baseline, daily from postoperative day 1 until hospital discharge, and then by phone at 1, 3, and 6 months postoperatively (Fig. 1 for trial schematic). Table 1 details the structured study summary according to the World Health Organization Trial Registration Data Set. The trial protocol was written in accordance with the Standard Protocol Items: Recommendations for Interventional Trials (SPIRIT) checklist [14] (Additional file 1).

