### Safety assessments and blinding

The Principal Investigator and other physician co-investigators will be in communication with the clinical team throughout the intra-operative period to ensure protocol adherence. Further criteria for withdrawal from the study preoperatively include active ongoing cardiac ischemia or acute decompensated arrhythmia, low oxygen saturation (SpO_2_ < 90%) on supplemental oxygen, or the use of continuous vasopressor or inotrope infusion medications. Patients will be withdrawn intraoperatively if they develop significant hemodynamic compromise because of cardiac surgery or sustained intra-operative oxygen desaturation (SpO_2_ < 90% for more than 3 minutes). At any time during the perioperative period patients may be withdrawn for significant physician or nursing concern.

Because real-time monitoring of protocol compliance requires knowledge of the patient’s assigned treatment, the study team utilizes a coordinated team approach. For every case, the study team members assessing the primary and secondary outcomes of the study will be blinded to the group assignment. This includes research staff administering neurocognitive assessments as well as physician staff monitoring patient progress and safety. The physician principal investigator is unblinded, and is responsible for conveying the treatment assignment to the clinical team and monitoring compliance with the assigned regimen intraoperatively. A trials specialist within the research group will monitor protocol compliance, occurrence and report any adverse events to the institutional review board (IRB).

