### Data analysis

Descriptive statistics of the data will be performed. Continuous data will be represented using mean (± standard deviation) or median (interquartile range) for variables not normally distributed and compared using parametric or non-parametric *t* tests as appropriate. Categorical data will be presented using proportions and compared using a chi-square (or Fisher’s exact) test. Two-sided *p* values less than 0.05 will be considered statistically significant. All analyses will be conducted using the intention-to-treat principle. No interim analyses are planned and there are no stopping rules for this trial. SAS 9.3 (SAS Institute, Cary, NC, USA) will be used for all analyses.

The primary outcome of the study is t-MoCA trajectories (values of t-MoCA) at postoperative day 2 between the two groups. An unadjusted *t* test (or non-parametric equivalent) will be used to assess superiority. Linear regression will be performed to identify independent predictors of t-MoCA as well as changes in t-MoCA over the 6-month study period. To account for the multiple measurements per subject, we will employ repeated measures regression techniques. Due to flexibility of timing of patient interviews, possibility of censored data and repeated observations, secondary analysis would require the use of a piecewise mixed-effects linear regression model measurement. Interaction will be assessed in the mixed-effects model to test if the t-MoCA slopes are different between groups.

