Secondary analysis of adverse events including incidence of delirium, stroke, myocardial infarction, acute kidney injury (AKI), and hypoxia will also be assessed by employing logistic regression or log-binomial regression for outcomes with an incidence of 10% or greater. Odds ratios or measures of relative risk will include 95% confidence intervals. Secondary outcomes including ADL and GDS values will also be assessed using a trajectory analysis, similar to that employed for t-MoCA scores over time. The harvested biological specimens will provide mechanistic data regarding impact of administered oxygen levels on plasma, urine, and tissue biomarkers. To test this, a linear mixed model will be used to estimate the trajectories of values over the study period. The treatment-by-time interaction will quantify differences in trajectories between the groups. Initial modeling will include participant-specific slope and intercepts with likelihood ratio tests of these variance components considered for model parsimony.

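### The 100 patients are defined as those who completed the intraoperative intervention, and patients can be withdrawn from the study during surgery; this conflicts with the stated intention-to-treat principle and leaves the day-2 comparison open to selection bias.

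*Protocol article*

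**What the plan says.** All references are to the protocol article.

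- **Sample size calculation.** The target is stated as "A total of 100 randomized subjects who have undergone the entire intraoperative intervention will be enrolled". The same sentence gives the reason for going above 74: an allowance for loss to follow-up or withdrawal.
- **Study design.** The trial is described as a "superiority trial of 100 participants with an allocation of 1:1". The Abstract and Table 1 also give 100, with no condition about completing the intervention.
- **Safety assessments and blinding.** "Patients will be withdrawn intraoperatively if they develop significant hemodynamic compromise because of cardiac surgery or sustained intra-operative oxygen desaturation"; the desaturation limit is SpO2 below 90% for more than 3 minutes. In addition, "At any time during the perioperative period patients may be withdrawn for significant physician or nursing concern". The paragraph introduces these as criteria for withdrawal from the study. The unblinded principal investigator tells the clinical team the assignment; outcome assessors and the physicians monitoring progress and safety are blinded.
- **Intervention and anesthesia regimen.** FiO2 is at least 0.35 in the normoxic arm, titrated up if saturation falls below 92%, and 1.0 throughout in the hyperoxic arm.
- **Data analysis.** "All analyses will be conducted using the intention-to-treat principle". The primary comparison is an unadjusted *t* test (or non-parametric equivalent) of t-MoCA at postoperative day 2. Secondary analyses cover "incidence of delirium, stroke, myocardial infarction, acute kidney injury (AKI), and hypoxia".

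**The concern.** Completing the intervention is something that happens after randomisation. A target defined by it sets aside patients whose surgery went badly enough for them to be withdrawn. An intention-to-treat label cannot undo this if withdrawal from the study means that no day-2 score is collected.

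The loss need not be balanced. Sustained desaturation is more plausible in an arm that starts at FiO2 0.35 than in one held at 1.0, and decisions during surgery are made by a team that knows the arm. If patients who desaturate would have scored lower, losing more of them from the normoxic arm raises that arm's observed mean. The primary test is unadjusted, so randomisation is its only protection. Hypoxia is also a planned outcome, and the patients with the most sustained hypoxia are among those to be withdrawn.

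**Working it through.** **1. The plan's own figure.** Inputs from Sample size calculation: difference 2, SD 3, "a two-sided α = 0.05 and 80% power", allocation 1:1. The standardised difference is 2/3. A two-sample *t* test (non-central *t*) needs 36.3 per arm, rounded up to 37, so 2 × 37 = 74. The stated 74 is reproduced and is not in dispute.

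**2. What the count means.** The allowance is (100 − 74)/100 = 26%. There are two readings.

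- *The 100 are all randomised patients* (Abstract, Study design, Table 1). Withdrawals during surgery come out of the 26%.
- *The 100 are completers* (literal wording of Sample size calculation). Withdrawals during surgery are additional, and the number randomised is unstated. With an assumed intraoperative withdrawal share w it is 100/(1 − w), rounded up: 106 (5%), 112 (10%), 118 (15%) or 125 (20%). The attrition allowance can then refer only to withdrawal after surgery.

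The sentence supports both readings: its definition points to completers, and its stated reason points to a margin that absorbs withdrawals.

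**3. Possible size of the bias.** The article gives no withdrawal rates and no scores for withdrawn patients, so everything in this step is assumed. Let wN and wH be the shares withdrawn in the normoxic and hyperoxic arms, and let withdrawn patients score d points below completers in their arm. The completer mean then exceeds the whole-arm mean by w × d, so

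bias = (wN − wH) × d.

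Under no true effect, the rejection rate of the two-sided 5% *t* test comes from the non-central *t* with non-centrality bias / (3 × √(2/n)). The standard error is 0.698 for n = 37 per arm and 0.600 for n = 50.

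| wN | wH | d | Bias (points) | Share of the 2-point target | Type I error, n = 37 | Type I error, n = 50 |
|---|---|---|---|---|---|---|
| 5% | 0% | 2 | 0.10 | 5% | 5.2% | 5.3% |
| 10% | 2% | 3 | 0.24 | 12% | 6.3% | 6.8% |
| 10% | 0% | 4 | 0.40 | 20% | 8.7% | 10.1% |
| 20% | 5% | 4 | 0.60 | 30% | 13.6% | 16.8% |

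Only the difference in rates matters: 15% against 5% with d = 4 also gives 0.40. In each row the bias favours normoxia, because each row assumes more withdrawals in that arm. With equal rates and equal deficits the bias is zero.

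**4. Can 100 randomised carry a full intention-to-treat analysis?** Power of the *t* test for a difference of 2 (SD 3), starting from 100 randomised:

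| Outcome lost | Patients analysed | Power |
|---|---|---|
| 0% | 100 | 91% |
| 10% | 90 | 88% |
| 20% | 80 | 84% |
| 26% | 74 | 81% |

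The planned number is enough without counting only completers.

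**The case against.** The strongest reply is that a completer analysis is stated nowhere. The article commits all analyses to intention-to-treat, never says that withdrawn patients lose follow-up or are dropped from analysis, and never says they are replaced. The target sentence itself says the 100 allow for withdrawal. As a condensed article, it may leave the handling of data after withdrawal to a fuller document. This stands as far as it goes: a reader might infer that withdrawn patients are certainly replaced and excluded, and the text does not establish that. It does not remove the conflict, because the article goes beyond silence. It defines the count by completion of the intervention and describes the withdrawals as withdrawals from the study.

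Further points narrow the concern:

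- Only desaturation is directly tied to the oxygen level. Haemodynamic compromise is attributed to the surgery, and staff concern is general.
- In the normoxic arm FiO2 is titrated up at a saturation above the withdrawal limit. This should reduce the difference between arms, though it need not remove it.
- A reader might infer that sustained hypoxia is missing from the safety comparison by construction. It is not: saturation is extracted every 30 seconds, so the event is recorded before withdrawal, and adverse events are monitored. Under-counting arises only if withdrawn patients are left out of the analysis.
- Physicians monitoring progress and safety are blinded, which weakens the concern about withdrawals after surgery more than about those during it.
- t-MoCA is not given to non-verbal ICU patients, so some of the sickest might have no day-2 score under any rule. The effect of the withdrawal rule alone may therefore be smaller than the formula gives.

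**Conclusion.** The point holds as a conflict between stated rules that can bias the primary comparison. The literal definition of the 100, together with withdrawal from the study during surgery, does not fit the intention-to-treat statement or the unconditional 100 in the Abstract, Study design and Table 1. The allowance for withdrawal leaves the count ambiguous.

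The consequence is conditional. If patients withdrawn during surgery are not assessed and analysed, selection bias is possible, probably favouring normoxia, with possible under-counting of sustained hypoxia. Its size cannot be derived from the article. The range of 0.1 to 0.6 points, with type I error of about 5.2% to 17%, rests on assumed differences in withdrawal of 5 to 15 percentage points and assumed deficits of 2 to 4 points. The low end is negligible and the high end is not, and the article gives no basis for choosing between them. The claim that the planned analysis is definitely a completer analysis goes further than the document allows.

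**What to change.** 1. **Sample size calculation:** state that 100 patients will be randomised and that patients withdrawn during surgery are not replaced. This also brings the section into line with the Abstract, Study design and Table 1.
2. **Safety assessments and blinding, and Data analysis:** reconcile the two and leave the clinical criteria as they are. State that a patient who meets a withdrawal criterion after randomisation continues t-MoCA and safety follow-up unless consent is withdrawn, and is analysed in the assigned arm.
3. **Hypoxia:** count intraoperative events in all randomised patients who have surgery.
4. **Reporting:** give withdrawals by arm with reasons, and present the completer set only as a sensitivity analysis.

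The cost is an amendment to wording, plus continued follow-up of the patients concerned. Including patients who left the assigned regimen dilutes the effect slightly; the power figures above show room for outcome losses of up to 26%. The article reports that recruitment is under way, so the change should be made soon: day-2 scores not collected cannot be recovered later.

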### Data analysis

Descriptive statistics of the data will be performed. Continuous data will be represented using mean (± standard deviation) or median (interquartile range) for variables not normally distributed and compared using parametric or non-parametric *t* tests as appropriate. Categorical data will be presented using proportions and compared using a chi-square (or Fisher’s exact) test. Two-sided *p* values less than 0.05 will be considered statistically significant. All analyses will be conducted using the intention-to-treat principle. No interim analyses are planned and there are no stopping rules for this trial. SAS 9.3 (SAS Institute, Cary, NC, USA) will be used for all analyses.

The primary outcome of the study is t-MoCA trajectories (values of t-MoCA) at postoperative day 2 between the two groups. An unadjusted *t* test (or non-parametric equivalent) will be used to assess superiority. Linear regression will be performed to identify independent predictors of t-MoCA as well as changes in t-MoCA over the 6-month study period. To account for the multiple measurements per subject, we will employ repeated measures regression techniques. Due to flexibility of timing of patient interviews, possibility of censored data and repeated observations, secondary analysis would require the use of a piecewise mixed-effects linear regression model measurement. Interaction will be assessed in the mixed-effects model to test if the t-MoCA slopes are different between groups.

Secondary analysis of adverse events including incidence of delirium, stroke, myocardial infarction, acute kidney injury (AKI), and hypoxia will also be assessed by employing logistic regression or log-binomial regression for outcomes with an incidence of 10% or greater. Odds ratios or measures of relative risk will include 95% confidence intervals. Secondary outcomes including ADL and GDS values will also be assessed using a trajectory analysis, similar to that employed for t-MoCA scores over time. The harvested biological specimens will provide mechanistic data regarding impact of administered oxygen levels on plasma, urine, and tissue biomarkers. To test this, a linear mixed model will be used to estimate the trajectories of values over the study period. The treatment-by-time interaction will quantify differences in trajectories between the groups. Initial modeling will include participant-specific slope and intercepts with likelihood ratio tests of these variance components considered for model parsimony.

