**Methods/Design:**

One hundred patients aged 65 years and older undergoing non-emergency coronary artery bypass grafting surgery on cardiopulmonary bypass will be enrolled in this prospective, randomized, controlled trial. Subjects will be randomized to receive a fraction of inspired oxygen of either 35% or 100% while under general anesthesia throughout the intraoperative period. The primary outcome measure will be the incidence of POCD in the acute postoperative phase and up to 6 months. The assessment of neurocognition will be undertaken by trained personnel, blinded to study group, with the telephone Montreal Cognitive Assessment (t-MoCA) tool. Secondary outcome measures will include assessment of delirium using the Confusion Assessment Method (CAM and CAM-ICU), as well as time to extubation, days of mechanical ventilation, length of ICU and hospital stay and mortality at 6 months. With the aim of later identifying mechanistic aspects of the effect of oxygen tension, blood, urine, and atrial tissue specimens will be taken at various time points during the perioperative period and later analyzed.

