**Fig. 1 Fig1:**
[figure not shown]
Study schema

**Table 1 Tab1:** WHO Trial Registration Data Set - Structured Summary

Data category	Information
Primary registry, trial identifying number	Clinicaltrials.gov Identifier - NCT02591589
Date of registration in primary registry	February 13, 2015
Secondary identifying numbers	
Sources of monetary support	Foundation for Anesthesia Education and Research Mentored Training Research Grant
Contact for public queries	SS, Department of Anesthesia, Beth Israel Deaconess Medical Center, Boston MA, USA
Contact for scientific queries	SS, Department of Anesthesia, Beth Israel Deaconess Medical Center, Boston MA, USA
Public title	Intraoperative Oxygen Concentration and Neurocognition After Cardiac Surgery
Scientific title	The relationship between administered oxygen levels and arterial partial oxygen pressure to neurocognition in cardiac surgical patients
Country of recruitment	USA
Health problem under investigation	Neurocognition after cardiac surgery
Key inclusion and exclusion criteria	Age ≥ 65 years, elective or urgent coronary artery bypass surgery (CABG) on cardiopulmonary bypass (CPB)
Study type	Interventional Allocation: randomized Interventional model: Masking: blinding of participant and outcomes assessor
Date of first enrollment	September 2015
Target sample size	100
Recruitment status	Recruiting as of January 2017
Primary outcome	Change in Telephonic Montreal Cognitive Assessment from baseline up to 6 months
Key secondary outcomes	Delirium incidence, time to extubation, Acute kidney injury incidence

The SPIRIT figure (Fig. 2) demonstrates the schedule of enrollment, interventions, and instruments of assessment used in the trial.

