## Study outcomes and their measurement

### Primary endpoint

To assess the occurrence of POCD we will use the t-MoCA. Scores on the t-MoCA will be measured preoperatively and postoperatively, using a daily in-hospital assessment until discharge or 30 days, whichever is sooner. In order to reduce fatigue completing assessments, if t-MoCA scores have plateaued for three consecutive days and CAM assessments are negative, assessments will occur every third day in-hospital through a skip pattern algorithm.

The t-MOCA is an adaptation of the widely used MoCA assessment [16], with items requiring writing and picture recognition removed. T-MoCA results in a 22-point scale and has been validated as a marker for cognitive function [16, 17]. Additionally, there will be telephone follow-up and t-MOCA assessment at 1, 3, and 6 months postoperatively, which does not require that participants be assessed in person. The telephonic version of the MoCA was chosen as the cognitive test to be performed both in-person and in telephonic follow-up so as to have equivalent scoring between assessments at all follow-up time points throughout the study. In previous studies, testing to 6 months has been shown to accurately reflect longitudinal follow-up of cognitive trajectories after CABG [18, 19] and thus this was the time endpoint for the follow-up in our study. Blinded, specially trained study staff will administer the assessments and assist in data collection.

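### Three different primary outcomes are named; the sample size and the superiority test serve only one of them, mean t-MoCA at postoperative day 2

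*Protocol article*

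**What the plan says.** Three places in the protocol article each define the primary outcome:

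- Abstract, Methods/Design: "The primary outcome measure will be the incidence of POCD in the acute postoperative phase and up to 6 months".
- Table 1 (WHO registration data set), primary outcome row: "Change in Telephonic Montreal Cognitive Assessment from baseline up to 6 months".
- Statistical analysis, Data analysis: "The primary outcome of the study is t-MoCA trajectories (values of t-MoCA) at postoperative day 2 between the two groups". An unadjusted t test or its non-parametric equivalent then assesses superiority.

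Two further sections do not settle the matter. Study design says "The primary outcome of postoperative cognitive decline will be assessed via cognitive testing at baseline, daily from postoperative day 1 until hospital discharge", and continues with telephone calls at 1, 3 and 6 months. Primary endpoint opens with "To assess the occurrence of POCD we will use the t-MoCA" and describes every assessment to 6 months without singling one out. The hypothesis in the Abstract and the objective at the end of the Background are also framed as POCD incidence.

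The Sample size calculation assumes "a two-sided α = 0.05 and 80% power" and is meant "to detect a mean difference in t-MoCA scores of 2 (standard deviation of 3") "between the hyperoxia and normoxia group at postoperative day 2". It arrives at 74 subjects, raised to 100 for attrition.

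**The concern.** The three definitions are not shorter and longer versions of one endpoint. The first is a yes/no event over a period, the second a within-patient change to 6 months, and the third a score on one day. The third is also inconsistent in itself, since a value on a single day is not a trajectory.

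The primary outcome decides what the trial may claim. The Abstract promises an answer on POCD incidence up to 6 months. The trial is sized and tested for mean cognition on day 2, the presumed low point. A day-2 mean difference cannot by itself support a statement about how many patients have POCD over 6 months. A null day-2 result would not refute that hypothesis either. A reader who takes the stated 80% power as covering the Abstract's hypothesis would be misled.

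**Working it through.** **1. The three definitions side by side**

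| Source | Variable | Time | Analysis given | Power given |
|---|---|---|---|---|
| Abstract | POCD, yes/no | acute phase to 6 months | only the general chi-square/Fisher rule for categorical data | none |
| Table 1 | change in t-MoCA from baseline | up to 6 months | regression of changes over 6 months; piecewise mixed model with a slope interaction, called secondary | none |
| Data analysis | t-MoCA score | day 2 | unadjusted t test for superiority | 80% with 74 subjects |

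**2. The plan's own figure**

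Inputs from the Sample size calculation: difference 2, SD 3, two-sided α 0.05, power 80%. Study design gives 1:1 allocation.

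- Normal approximation: n per arm = 2 × (1.960 + 0.842)² × 3² / 2² = 35.3, so 36 per arm and 72 in total.
- Noncentral t: 36.3, so 37 per arm and **74 in total**, which matches the article. Power at 37 per arm is 80.8%.
- With all 100 analysed, power for the same day-2 comparison is 91%. The step from 74 to 100 allows 1 − 74/100 = 26% attrition.

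The arithmetic is sound. No incidence, risk difference, change-score SD or 6-month effect enters it.

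**3. If POCD incidence were primary (illustration)**

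Assumptions: control rates at the Background's upper figures (50% at discharge, 30% at 6 months), and a halving by the intervention. The halving is mine; the article gives no expected difference in incidence.

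Power = Φ{ [ |p₁ − p₂|√n − 1.96√(2p̄(1 − p̄)) ] / √(p₁(1 − p₁) + p₂(1 − p₂)) }

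- 50% against 25%, n = 50 per arm: (0.25 × 7.071 − 1.96 × 0.6847) / 0.6614 = 0.644, power **74%**. With 37 per arm, 61%.
- 30% against 15%, n = 50 per arm: (0.15 × 7.071 − 1.96 × 0.5906) / 0.5809 = −0.167, power **43%**. With 37 per arm, 34%.
- Smaller relative reductions of 25% to 40% give 24% to 53% power from 50%, and 13% to 29% from 30%, with 100 patients.
- For 80% power with 50 per arm, incidence must fall from 50% to about 23%, or from 30% to about 8%.

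**4. If change from baseline were primary (illustration)**

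Assumptions: SD 3 at each visit and a 2-point difference that persists. The SD of change is 3√(2(1 − ρ)), with ρ the correlation with baseline, which the article does not give.

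| ρ | SD of change | Power, 74 patients | Power, 100 patients |
|---|---|---|---|
| 0.3 | 3.55 | 67% | 80% |
| 0.5 | 3.00 | 81% | 91% |
| 0.7 | 2.32 | 95% | 99% |

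If the difference shrinks after day 2 (SD kept at 3), power with 74 and 100 patients is 56% and 70% at 1.5 points, and 29% and 38% at 1 point.

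**The case against.** The strongest reply is that the operative statistical text is consistent. The Sample size calculation and the Data analysis section agree on day 2, the mean t-MoCA and one unadjusted test, and the mixed model is called secondary. A statistician following those sections would know what to run. This stands, and it rules out several stronger readings:

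- A reader might infer that success could be claimed from any of three equally eligible outcomes, with a calculable inflation of the 5% error rate. The documents do not support this. Only one outcome has a stated superiority test, and the article sets out no family of competing primary tests from which an error rate could be computed.
- A reader might infer that the 6-month change has no planned analysis. It has regression and a mixed model; what it lacks is a power calculation and primary status in the analysis.
- A reader might infer that 80% power is out of reach for anything but day 2. The change-score table above shows otherwise under favourable assumptions.
- A reader might infer that the registry entry is wrong. The registry record is not shown; only Table 1 is.

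The incidence figures are also open to challenge. The Background rates are ceilings, and this article states no t-MoCA cut-off for POCD, so the rates may not carry over to a t-MoCA-based definition. They are illustrations only.

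The contradiction itself remains. Condensing a protocol into an article does not turn one endpoint into three, and an unseen analysis plan could choose among these statements but would not make them agree.

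**Conclusion.** Wrong as written. The article contradicts itself on its primary outcome, and this must be fixed because it determines the trial's headline claim. The figure of 74 is correct, but it supports only the day-2 mean comparison. POCD incidence, the subject of the Abstract's hypothesis, has no power calculation and only a generic test. The 6-month change in Table 1 has an analysis but no power calculation.

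The size of the gap depends on assumptions that the article does not supply. For incidence, power with 100 patients is about 74% or 43% under a halving from the ceiling rates, and lower for smaller effects. For a change score, about 80% is kept with 74 patients only if the baseline correlation is about 0.5 or more and the full 2-point difference lasts. The finding itself rests on the wording and does not depend on these illustrations.

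**What to change.** Name one primary outcome everywhere: t-MoCA score at postoperative day 2, compared as a between-arm mean difference. It is the least disruptive choice because it alone has both a sample size and a superiority test.

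- Make the Abstract, Study design, Table 1, Primary endpoint and Data analysis agree, and delete the word trajectories from the primary definition.
- Make POCD incidence and the 1-, 3- and 6-month t-MoCA secondary.
- State that the 80% power and the primary conclusion concern day-2 cognition only, and align the hypothesis (Abstract) and objective (Background) with this.
- Check the registry entry. If it differs, correct it by a dated, justified amendment made before any results by arm are seen.

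If the sponsor prefers incidence or 6-month change as primary, the sample size must be justified for that outcome instead.

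Cost: no new data, but the headline claim narrows from POCD over 6 months to cognition on day 2. Enrolment began in September 2015 and was still open in January 2017, so this is a mid-trial amendment. No interim analysis is planned, which makes it feasible to complete before outcome data are compared.
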